**Discussion:**

It is important to develop a greater understanding of the emotional factors which may underlie key social deficits in stroke recovery in an ageing population where stroke is one of the leading causes of severe, complex disability. This research may enable us to identify those who are risk of participation restriction and target them in the acute stroke phase of stroke so that adverse outcome is avoided and rehabilitation potential is fulfilled.

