### Aims and objectives

Therefore, this research aims to explore three different facets of emotion processing following stroke, exploring which difficulties in emotion processing occur and how these impairments impact on social participation in stroke survivors, while controlling for levels of activity limitation.

Participants will complete measures twice, at approximately one month post stroke and one year thereafter. This will allow the examination of the extent to which impairments in emotion processing are associated with social participation at both acute and chronic phases of stroke recovery. Also, by assessing participants longitudinally, direction of causation between emotion processing difficulties and social participation limitations can be explored.

The specific research questions which we will address are:

1) During the acute phase, approximately one month post-stroke, are deficits in emotion processing correlated with levels of social participation?

2) During the chronic phase, approximately one year post-stroke, are deficits in emotion processing correlated with social participation?

3) do emotion processing deficits in the acute phase of stroke predict social participation at one year post stroke which is not accounted for by activity limitation?

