## Methods

### Design

This is a predictive study with a prospective design. Measures of emotion processing and social participation administered at baseline will be used to predict participation outcome at one year post stroke.

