### Analysis

Initially, a correlational analysis will be conducted on the measures from each domain of emotion processing to ascertain if the measures within that domain are highly correlated with each other. If this is the case the measures will be amalgamated. The same process will be conducted with the measures of social participation. Should the measures not be highly correlated an exploratory factor analysis will be conducted.

Regression analyses will be conducted to investigate whether the emotion processing measures predict social participation measures, controlling for activity limitations. The final research question was whether emotion processing deficits in the acute phase of stroke predict social participation at one year post stroke which is not accounted for by activity limitation? To address this, hierarchical regression analyses will be conducted, predicting social participation at second assessment from concurrent activity limitation in the first step and emotion processing from the acute phase of stroke entered in the next step of the regression.

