## Discussion

### Potential implications of work

This project will address a number of health care service priorities, including stroke, mental health, ageing and quality of life. This research has the potential to improve knowledge of the effects of stroke on mood and emotion perception, as well as enhancing our knowledge of the relationship between emotion processing constructs and participation outcome. Improving our understanding of the emotional factors which may underlie key social deficits in stroke is important to inform models of functioning and disability following stroke, as factors other than activity and cognitive limitations may be important in influencing post-stroke outcomes.

The results from these studies will be of interest not only to the academic community with an interest in ageing and health outcomes, but also to both medical groups and patient support groups with an interest in stroke. In the longer term, the results from this study may influence future practice within rehabilitation settings. If emotion processing difficulties predict participation levels and activity limitation, then those individuals could potentially be targeted for intervention in the acute stroke phase, ensuring that rehabilitation potential is fulfilled. Interventions have previously been successful in improving recovery in stroke patients. A randomised controlled trial of an intervention to increase patients’ perceived control over their recovery resulted in better recovery from activity limitations [45]. Interventions targeting emotional states in the acute phase of stroke have been found to improve quality of life outcomes [30]. This research is also important in combining theoretical and applied scientific approaches from health psychology and cognitive neuroscience to important health problems.

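### The only specified model for research question 3 adjusts for one-year activity limitation, so it cannot show whether acute emotion processing adds to activity limitation known at one month

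*Protocol article*

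**What the plan says.** The protocol article's Analysis section specifies one model for research question 3: a hierarchical regression "predicting social participation at second assessment from concurrent activity limitation in the first step and emotion processing from the acute phase of stroke". The words that matter here are "from concurrent activity limitation in the first step". Under Aims and objectives, the question concerns "social participation at one year post stroke which is not accounted for by activity limitation". It does not say at which visit activity limitation is to be taken.

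Three other places say what the result is for:
- The Design section states: "Measures of emotion processing and social participation administered at baseline will be used to predict participation outcome at one year post stroke".
- The Discussion part of the abstract states: "This research may enable us to identify those who are risk of participation restriction and target them in the acute stroke phase of stroke".
- Potential implications of work states: "If emotion processing difficulties predict participation levels and activity limitation, then those individuals could potentially be targeted for intervention in the acute stroke phase".

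The Measures and Procedure sections have the whole battery given at both visits. The mFLP activity-limitation categories are therefore available at one month as well as at one year. The article gives no reason for choosing the one-year value and describes no second model for this question that uses the one-month value.

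**The concern.** The predictor is measured at one month. The step 1 covariate is measured at one year, at the same visit as the outcome. Two consequences follow.

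First, a model that needs a one-year value cannot be applied at one month. It also does not test whether emotion processing tells the clinician more than the activity limitation already observed then. This needs no causal assumption.

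Second, the article itself allows that emotion processing may predict activity limitation. If so, one-year activity limitation lies on the pathway, and conditioning on it takes out the part of the association that passes through it. Conditioning on a variable that follows the predictor can also distort what remains, if one-year activity limitation and participation share causes that were not measured. That matters because the Aims section hopes that "direction of causation between emotion processing difficulties and social participation limitations can be explored".

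At stake is whether a null or small result in step 2 would be taken as evidence that acute emotion processing is of no use for early identification. The planned model cannot support that conclusion.

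**Working it through.** **1. Timing, side by side.**

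| Element of the research question 3 model | Visit | Source |
|---|---|---|
| Outcome: social participation | one year | Analysis |
| Step 1: activity limitation | one year (concurrent with the outcome) | Analysis |
| Step 2: emotion processing | one month | Analysis |
| Activity limitation available but not used | one month | Measures; Procedure |
| Intended use of the result | acute phase | Abstract; Potential implications of work |

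The general sentence in Analysis about controlling for activity limitations gives no visit, so it does not supply the missing model.

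**2. The article's own figure.** Sample size gives 119 for an F test with a medium effect, alpha 0.05 and power 0.95. I assume f² = 0.15 for medium, the usual regression convention; the article does not give the value. The noncentrality is f² × N = 0.15 × 119 = 17.85. With three tested predictors the smallest N is exactly 119 (power 0.951). With 1, 2, 4 or 5 tested predictors it would be 89, 107, 129 or 138. Adding 1 to 4 activity-limitation covariates leaves it at 119. The choice of visit for the covariate therefore does not change the stated sample size.

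**3. What each model estimates.** This is an illustration; no path value below is in the documents. Let E be one-month emotion processing, A1 and A2 activity limitation at one month and one year, and P one-year participation, all standardised and scored in the same direction.

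- A2 = 0.5·A1 + a·E + error
- P = b·A2 + c·E + error

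Substituting the first line into the second gives P = (c + a·b)·E + 0.5·b·A1 + error. Adjusting for A1 therefore gives E the coefficient c + a·b. Adjusting for A2 gives c. The difference is a·b.

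Power is for a one-degree-of-freedom test at N = 119 and alpha 0.05, with an assumed correlation of 0.3 between E and A1 and no other confounding.

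| c | a | b | Adjusting for A1: coefficient (power) | Adjusting for A2: coefficient (power) |
|---|---|---|---|---|
| 0 | 0.2 | 0.3 | 0.06 (0.096) | 0 (0.050) |
| 0 | 0.4 | 0.5 | 0.20 (0.601) | 0 (0.050) |
| 0.1 | 0.3 | 0.5 | 0.25 (0.805) | 0.10 (0.212) |
| 0.2 | 0.2 | 0.3 | 0.26 (0.813) | 0.20 (0.605) |
| 0.2 | 0 | 0.3 | 0.20 (0.576) | 0.20 (0.640) |
| 0.2 | 0 | 0.5 | 0.20 (0.601) | 0.20 (0.737) |

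The first two rows show that the models answer different questions. With no direct effect, the one-month model still finds an association, and the concurrent model correctly reports that none is left once one-year activity limitation is accounted for. In the last two rows a = 0, so nothing is lost, and the planned model has slightly more power.

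**4. Shared unmeasured cause.** Add to both equations a variable U with path u, unit variance, and independent of E and A1. Adjusting for A2 then gives c − u²·k / (V − k²), where k = a + 0.5·r, r is the correlation of E with A1, and V is the variance of A2. Take c = 0.20 and u = 0.4:

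- a = 0.2, r = 0, unit error variances: k = 0.2, V = 0.25 + 0.04 + 0.16 + 1 = 1.45. The coefficient is 0.20 − 0.16 × 0.2 / 1.41 = 0.18.
- a = 0.3, r = 0.5, V = 1: k = 0.55. The coefficient is 0.20 − 0.16 × 0.55 / 0.6975 = 0.07.

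Under these assumptions the planned model could return anything from about 0.07 to 0.18 for a direct effect of 0.20. The spread comes from the correlation, the path a and the error scaling, none of which the documents give.

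**The case against.** The strongest reply is that the model does what the question asks. The aim is prediction beyond activity limitation, and the Background argues that activity limitation alone does not explain lost participation after stroke. On that reading, one-year participation should be set against one-year disability, and removing what runs through it is the purpose of the model. This stands. It is the natural reading of the question, and the planned model should be kept for it.

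A reader might go further than the documents allow in two ways. One is to infer that the planned model is simply wrong and that independence from activity limitation should be read from a one-month model instead. With a zero direct effect, a = 0.2 to 0.3 and b = 0.4 to 0.5, the one-month model gives 0.2 × 0.4 = 0.08 to 0.3 × 0.5 = 0.15. It would call independent an association that is wholly accounted for by one-year activity limitation.

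The other is to put a percentage on the loss. With a direct effect of 0.20 and the same paths, one obtains 0.08/0.28 = 29% to 0.15/0.35 = 43%, but these figures only restate the paths that were assumed.

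It can also be said that the targeting statements are conditional and look to the future, that no scoring tool is planned, and that the Design sentence names emotion processing and participation, not activity limitation, as the baseline predictors. That lowers the weight of the point. It does not supply an analysis that would support those statements, and the direct-effect reading is itself only safe if there are no important shared unmeasured causes.

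**Conclusion.** The point holds in a limited form. The model specified for research question 3 is a defensible estimate of the association that does not run through one-year activity limitation, provided that one-year activity limitation and participation share no important unmeasured cause. It does not address whether acute emotion processing adds to activity limitation known at one month, so the acute-phase prediction and targeting aims have no specified analysis behind them. That gap follows from the timing alone.

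No size can be given from the documents. In a linear model with activity limitation measured without error, the difference between the two adjusted coefficients is the product of two unknown paths. It is zero if emotion processing has no effect on later activity limitation. Bias from shared causes is possible but hypothetical. The stated sample size is unaffected.

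**What to change.** Add to the Analysis section a second hierarchical model for research question 3: one-year participation as outcome, one-month mFLP activity limitation in step 1, and acute-phase emotion processing in step 2. State that conclusions about acute-phase prediction and targeting rest on this model.

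Keep the concurrent-activity model. Label it as the direct association not running through one-year activity limitation, and answer the question of prediction beyond activity limitation from it, with a caveat about shared unmeasured causes.

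The one-month measure is already collected, so no new data or patients are needed. The cost is a few sentences of wording and one additional model to report.

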## Discussion

### Potential implications of work

This project will address a number of health care service priorities, including stroke, mental health, ageing and quality of life. This research has the potential to improve knowledge of the effects of stroke on mood and emotion perception, as well as enhancing our knowledge of the relationship between emotion processing constructs and participation outcome. Improving our understanding of the emotional factors which may underlie key social deficits in stroke is important to inform models of functioning and disability following stroke, as factors other than activity and cognitive limitations may be important in influencing post-stroke outcomes.

The results from these studies will be of interest not only to the academic community with an interest in ageing and health outcomes, but also to both medical groups and patient support groups with an interest in stroke. In the longer term, the results from this study may influence future practice within rehabilitation settings. If emotion processing difficulties predict participation levels and activity limitation, then those individuals could potentially be targeted for intervention in the acute stroke phase, ensuring that rehabilitation potential is fulfilled. Interventions have previously been successful in improving recovery in stroke patients. A randomised controlled trial of an intervention to increase patients’ perceived control over their recovery resulted in better recovery from activity limitations [45]. Interventions targeting emotional states in the acute phase of stroke have been found to improve quality of life outcomes [30]. This research is also important in combining theoretical and applied scientific approaches from health psychology and cognitive neuroscience to important health problems.
